### Randomisation

Participants are randomised (2:1) to the intervention or control group stratified by sex, time since treatment completion (≤12 months, >12 months), and meditation experience (yes/no). A random sequence will be generated for each one of the eight strata using block randomisation. For every three participants enrolled in each stratum, two will be allocated to the intervention group and one to the control group. Random sequences will be embedded in the online system, ensuring allocation concealment. Study personnel will not have access to the sequences and will be blind to group assignment. After randomisation, participants will be unblinded to group assignment, as the intervention does not allow for blinding. All questionnaires will be completed online, which will reduce the influence of researcher bias. Given the nature of the intervention and the context in which participants are recruited, i.e. outpatient clinic, we cannot rule out the usual risks of bias due to participants not being blinded to treatment allocation. However, in this study, all surveys will be completed online; health practitioners have no involvement in the collection or assessment of any of the trial outcomes. Unequal randomisation, where the number of participants allocated to the intervention group exceeds that in the control group, has been identified as a suitable approach in early-phase studies where the aim is to explore various dimensions of the intervention, such as patterns and frequencies of usage [34].

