### Sample size

We aim to enrol 75 participants over a 5-month period. The target sample size of 75 participants (50 in the intervention group, 25 in the control group) meets recommendations for pilot studies aimed at evaluating feasibility and estimating variance to inform sample size and power calculations for a main trial [57]. The 5-month recruitment period was informed by (1) screening past melanoma clinic lists for eligible patients at the cancer centre over a period of 3 months, (2) findings from a survey-based study among people with melanoma [28], and (3) an estimated 70% participation rate based on findings from online mindfulness-based pilot studies for patients with cancer [29, 58] (Fig. 1).

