### Analysis plan

Descriptive statistics will be used to present participants’ characteristics. Demographic and clinical characteristics, and experience with meditation will be compared between intervention and control groups, using *t* test or Wilcoxon rank-test (for continuous variables) depending on the outcome distribution and chi-square or Fisher’s exact test (for categorical variables).

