#### Primary objective—feasibility

Descriptive statistics will be used to present feasibility data. The overall study feasibility will be assessed through the following measures:Proportion of people approached (target: 80%): number of people approached as a proportion of those meeting clinical eligibility. Reasons for not approaching will be summarised.Proportion of people eligible for the study (target: 65%): number of people meeting all eligibility criteria as a proportion of those approached. Reasons for non-eligibility criteria and declining participation will be summarised.Proportion of people enrolled (target: 45%): number of people completing the baseline questionnaire as a proportion of those eligible.Completion rate (target: 70%): number of participants completing the end-of-study assessment as a proportion of those enrolled. It will not be possible to capture reasons for non-completion as there will be no interaction between the researcher and participants once they are enrolled in the study.

The intervention feasibility will be assessed through the following measures:Meditation adherence rate (target: 70%): number of guided meditations listened to per week over the total number of meditation sessions scheduled (14 sessions/week)Rate of adherence to weekly sessions (target: 50%): the number of videos viewed over the total number of videos scheduled per weekEngagement with the intervention: recording website navigation patterns and features used (video, audio and document downloads)Content relevance: type of benefits experienced and aspects of the program most liked and disliked (data collected through weekly questionnaires)

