#### Secondary objectives—potential efficacy of intervention on outcome measures

To explore the potential efficacy of the intervention on any of the secondary outcomes (i.e. fear of cancer recurrence, worry, rumination, perceived stress and trait mindfulness), a linear mixed model will be fitted including group (intervention, control), time (pre, post) and the interaction group by time as fixed effects and participant as a random effect. We will additionally adjust for any characteristics or scores showing clear evidence of imbalance at baseline. All analyses will be undertaken on an intention-to-treat (ITT) basis, i.e. participants will be analysed as randomised regardless of adherence.

In addition, potential association between overall meditation time and the secondary outcome measures will be assessed in the intervention group. Weekly meditation time will be defined as the maximum between time collected from Google Analytics and time self-reported in the weekly questionnaires.

Results of this study will be prepared in accordance with the CONSORT 2010 statement: extension to randomised pilot and feasibility trials [59].

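### Covariates for the secondary-outcome model are to be picked from observed baseline imbalance, a rule that almost never brings in the three randomisation strata the model omits

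*Protocol article*

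**What the plan says.** In the protocol article, *Randomisation* sets a 2:1 allocation stratified by sex, time since treatment completion (up to 12 months or longer) and meditation experience (yes or no): "A random sequence will be generated for each one of the eight strata using block randomisation". Within each stratum, "For every three participants enrolled in each stratum, two will be allocated to the intervention group and one to the control group".

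*Secondary objectives—potential efficacy of intervention on outcome measures* gives the model as group, "time (pre, post) and the interaction group by time as fixed effects and participant as a random effect". No stratification factor is among the terms. The section then adds: "We will additionally adjust for any characteristics or scores showing clear evidence of imbalance at baseline".

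The opening paragraph of *Analysis plan* states that "Demographic and clinical characteristics, and experience with meditation will be compared between intervention and control groups", by t or Wilcoxon tests for continuous variables and chi-square or Fisher tests for categorical ones. Meditation experience, one of the compared variables, is itself a stratification factor.

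*Aims and objectives* makes effect-size and variance estimates for the main trial an explicit secondary objective.

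**The concern.** The rule for choosing covariates has three faults.

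- **It looks at the wrong property.** Under sound randomisation, baseline differences between arms arise by chance, so a test of them examines a null hypothesis known to be true. A variable earns its place in the model by predicting outcome, and imbalance says nothing about that.
- **It works against the design.** The three factors judged important enough to stratify on are the ones that blocking keeps balanced. A trigger based on imbalance will pass over them.
- **It is open-ended.** There is no criterion for clear evidence and no candidate list. The word *scores* may also take in the baseline value of the outcome being analysed, which is already the pre response in the mixed model and would then be used twice.

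At stake is whether the estimates handed to the main trial come from a model fixed in advance or from one shaped by chance and judgement on 75 participants.

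**Working it through.** **1. Design figures.** From *Sample size* and *Randomisation*: 75 × 2/3 = 50 and 75 × 1/3 = 25; 2 × 2 × 2 = 8 strata. Both agree with the text. No alpha, power, effect or SD is stated, so there is no power figure to reproduce.

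**2. Would the rule select the strata?** Simulation of 3,000 trials with n = 75, 2:1 allocation and blocks of three within eight strata. Factor prevalences of 45%, 35% and 35% are assumed.

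- Any of the three stratification factors with chi-square p < 0.05: 0 of 3,000 trials.
- An unstratified binary variable: 5.9%.

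**3. How often would something be flagged by chance?** *Data collection* lists five demographic variables, meditation experience, and about four clinical items (stage, dates, treatment types, time since treatment), so about 10. The five questionnaire scores bring this to about 15. Removing the three strata leaves 12. For m independent variables, P(at least one flag) = 1 − (1 − α)^m. The level and the independence are assumptions.

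| m | α = 0.05 | α = 0.10 |
|---|---|---|
| 10 | 1 − 0.95^10 = 40% | 65% |
| 12 (without strata) | 1 − 0.95^12 = 46% | 1 − 0.90^12 = 72% |
| 15 | 1 − 0.95^15 = 54% | 79% |

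**4. Does leaving out the strata inflate the standard error of the group-by-time contrast?** Assume unit residual SD and a pre-post correlation of 0.6, so the within-person variance is 0.4. With complete data the contrast is a difference in mean change, in which any time-constant term cancels:

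SE = √[2 × 0.4 × (1/50 + 1/25)] = √0.048 = 0.219 SD.

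The simulation (each factor worth 0.3 SD) agrees:

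| Setting | Without strata | Strata main effects | Strata and strata-by-time |
|---|---|---|---|
| Complete data, mean SE | 0.219 | 0.219 | 0.220 |
| 30% missing post scores, mean SE | 0.256 | 0.256 | 0.258 |
| 30% missing, strata also shift change by 0.3 SD each, empirical SD | 0.266 | 0.262 | 0.260 |

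The 30% missing comes from the 70% completion target. With complete data, strata main effects leave the estimate exactly as it was. With 30% missing it moves by 0.016 SD on average (maximum 0.09), or by 0.020 (maximum 0.13) when strata also affect change. In that last case the spread falls by 0.266/0.260 − 1, about 2%.

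**5. A limit on step 4.** The mixed-model simulation treated the variances as known. If strata affect change and the residual variance is estimated without them, the reported SE absorbs their contribution. With independent factors this is 0.09 × (0.45 × 0.55 + 2 × 0.35 × 0.65) = 0.063, added to a change variance of 0.8. Then √(0.863/0.8) = 1.04, or about 4% too wide with complete data. This is still small.

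**The case against.** The affected outcomes are exploratory, in a feasibility study whose primary results are descriptive proportions that this rule does not touch. The trigger uses baseline data only and never sees the treatment effect. A covariate entered as a main effect hardly moves the group-by-time estimate, whether it was chosen by chance or not. All of this stands, and it limits the importance of the point.

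A condensed article may leave stratification covariates to a fuller document. That is fair as to the strata alone. But the article does more than stay silent: it fixes a selection rule, and that rule will not reach the strata.

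The article does not tie its notion of clear evidence to the baseline tests or to a 5% level, and those tests do not list the questionnaire scores. The link is an inference. Clinical variables such as stage, dates and treatment types are also related, which would lower the flag probabilities, while a looser reading of the rule would raise them.

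A reader might infer a larger harm: that ignoring strata which explain 10% to 20% of residual variance makes the standard error 1/√(1 − R²) = 1.05 to 1.12 times too wide. That formula suits a comparison at a single time point. In the stated pre/post model it would need the strata to explain that share of the variance in *change*, and nothing in the document supports this.

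**Conclusion.** The point holds as a fault of pre-specification. The protocol article commits to choosing covariates from observed imbalance, without a criterion, and its stated model leaves out the three stratification factors, which that rule will almost never restore. To say that the rule guarantees their exclusion would go slightly too far, because incomplete blocks allow small imbalances.

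The chance of at least one flagged variable is about 40% to 54% at an assumed 5% level with 10 to 15 independent variables. The effect on the group-by-time contrast is small: no change with complete data when strata act only as main effects, and about 2% in spread when they also affect change. These results rest on the assumed correlation, prevalences and 0.3 SD effects. Only the complete-data cancellation of main effects holds whatever their size.

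The consequence is a covariate set settled after the data are seen, and so less reproducible estimates for planning the main trial. The document does not support a claim of serious bias or material loss of power.

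**What to change.** - Delete the imbalance-triggered adjustment and the between-arm baseline tests. Report baseline characteristics and scores descriptively by arm.
- Pre-specify one model for every secondary outcome: the 6-week score on group, adjusted for the baseline score and for sex, time since treatment completion and meditation experience as main effects. At 70% completion there would be about 0.70 × 75 = 52 participants (35 and 17 to 18 per arm), so three main effects are preferable to eight stratum cells.
- Alternatively, keep the pre/post mixed model and add the three factors with their time interactions (six extra parameters). Do not also enter the baseline score as a covariate, since it is already a response.
- Label any other adjustment as sensitivity analysis.

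Under the assumptions above, the post-score model also has the smaller spread before any strata are added: 0.202 against 0.219 SD with complete data, and 0.237 against 0.253 with 30% missing. That gain comes from conditioning on the baseline score.

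The cost is wording and a few degrees of freedom. All variables are already collected and the sample size stays at 75. The post-score model needs a stated way to handle participants without a 6-week score, because the mixed model keeps their baseline data and a simple post-score regression drops them.

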### Aims and objectives

The overall aim of the study is to examine the feasibility and acceptability of an online mindfulness-based program among people who have completed treatment for melanoma.

The primary objective of the study will be to assess the feasibility of conducting a larger scale randomised control trial by evaluating:Overall recruitment, retention and questionnaire completion ratesAdherence to, and usability and acceptability of, the online program

The secondary objectives will be to assess the potential benefit of the intervention on fear of cancer recurrence, worry, rumination, perceived stress and trait mindfulness compared to a usual-care group and to provide effect size and variance estimates for these outcomes to inform the design of a larger clinical trial.

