## Methods/design

### Design

The development of the study protocol followed the SPIRIT (Standard Protocol Items: Recommendations for Interventional Trials) guidelines [30] (Additional file 1). The description of the intervention followed the TIDieR (Template for Intervention Description and Replication) guidelines [31] (Additional file 2).

This study is a single-centre, randomised controlled pilot study. The control group will continue to receive care from their treatment centre as usual, while participants in the intervention group will receive access to a 6-week online mindfulness program as well as their usual care. The groups will be compared to assess the potential effect of the intervention on a series of outcome measures. Measurements will take place at baseline (i.e. before randomisation) and at the end of the study (i.e. 6 weeks after randomisation). In the intervention group, participant engagement with, and usability and acceptability of, the program will be assessed weekly through a short questionnaire. The overall design and participant flow through the trial is illustrated in Fig. 1.

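### As worded, the imbalance rule lets an outcome's own baseline score be both response and covariate in one mixed model, which collapses the model's variance estimate and understates the standard error

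*Protocol article*

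**What the plan says.** In the protocol article, the section on secondary objectives within the Analysis plan specifies, for each of five outcomes, a model "including group (intervention, control), time (pre, post) and the interaction group by time as fixed effects and participant as a random effect". The Design section fixes two occasions: "Measurements will take place at baseline (i.e. before randomisation) and at the end of the study (i.e. 6 weeks after randomisation". Each participant therefore contributes at most two responses per outcome, and the baseline score is one of them.

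The same section then states: "We will additionally adjust for any characteristics or scores showing clear evidence of imbalance at baseline". The scores described under Outcome measures are the five questionnaires for fear of recurrence, rumination, worry, mindfulness and stress. No text excludes an outcome's own baseline score from the rule, and none says that the pre rows are dropped when a baseline score becomes a covariate.

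Under Aims and objectives, a secondary purpose of the pilot is to "provide effect size and variance estimates for these outcomes to inform the design of a larger clinical trial".

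**The concern.** For the outcome being modelled, the pre response and the proposed covariate are the same number. The covariate predicts the pre rows closely but the post rows only partly. A random-intercept model with one residual variance cannot represent that: it pools small pre residuals with real post residuals, and the participant variance is driven to its lower bound of zero.

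Two things are at stake. The interval around the group-by-time effect becomes too narrow, and the model's variance components can no longer serve the objective of informing the main trial. The problem concerns only an outcome's own baseline score. Age, stage, or a different questionnaire's score is an ordinary covariate and is unaffected.

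**Working it through.** **Inputs from the article.** 50 and 25 participants (Sample size), two visits (Design), the model and rule quoted above, and a 70% completion target (feasibility measures).

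**Assumptions.** The article gives no SD, pre-post correlation or imbalance threshold. I take SD s = 1 at both visits, correlation r = 0.3 to 0.8, no true effect, week-6 scores missing at random and, where a trigger is needed, baseline p<0.05. There is no stated figure to reproduce.

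**Algebra, complete data.**

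1. The within-person change has variance 2s²(1−r), so the residual variance is s²(1−r).
2. Given the baseline score, the person mean has variance s²(1−r²)/4.
3. The implied participant variance is s²(1−r²)/4 − s²(1−r)/2 = −s²(1−r)²/4. This is negative for every r<1, so the estimate is set to zero.
4. The residual variance then pools to [s²(1−r) + s²(1−r²)/2]/2 = s²(1−r)(3+r)/4.
5. The interaction SE is multiplied by √[(3+r)/4].

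At r = 0.5 the pooled variance is 0.5 × 3.5/4 = 0.4375 and the SE factor is √0.875 = 0.935. The interaction SE falls from √[2 × 0.5 × (1/50 + 1/25)] = 0.245 to √[2 × 0.4375 × 0.06] = 0.229.

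**REML simulation, 2,000 trials per setting, own baseline score always added.** The true total variance is 1.00; without the covariate the model returns 0.995 to 1.005. The SE ratio is with versus without the covariate.

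| r | Total variance, complete (formula / simulated) | Total variance, 70% completion | SE ratio, complete (formula / simulated) | SE ratio, 70% completion |
|---|---|---|---|---|
| 0.3 | 0.578 / 0.576 | 0.490 | 0.908 / 0.911 | 0.817 |
| 0.5 | 0.438 / 0.435 | 0.366 | 0.935 / 0.937 | 0.823 |
| 0.7 | 0.278 / 0.278 | 0.228 | 0.962 / 0.963 | 0.826 |
| 0.8 | 0.190 / 0.191 | 0.157 | 0.975 / 0.976 | 0.830 |

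The participant variance was estimated at zero in 95-100% of these trials, and in 92-96% of a smaller set (250 trials per setting, r = 0.5). The shortfall is larger with missing data because participants without a week-6 score still contribute a closely predicted pre row. The model without the covariate had SEs within about 3% of the empirical SD, so the shrinkage is an error and not a gain in precision.

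**Point estimate.** With complete data the covariate is constant within a person and the interaction rests on within-person change. The estimate was identical with and without the covariate (largest difference 0.0000). In trials with baseline p<0.05, the bias from regression to the mean was −0.282 SD (r = 0.5) and −0.161 SD (r = 0.7) in both models. At 70% completion individual estimates move, but the average bias does not: −0.286 without and −0.284 with the covariate at r = 0.5.

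**False rejection at nominal 5%, only trials with baseline p<0.05 (800 per setting).**

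| Completion | r | Without covariate | With covariate | Week-6 score, baseline as covariate |
|---|---|---|---|---|
| 100% | 0.5 | 19.4% | 22.8% | 5.0% |
| 100% | 0.7 | 12.5% | 14.6% | 5.1% |
| 70% | 0.5 | 16.9% | 26.6% | 5.0% |
| 70% | 0.7 | 11.9% | 19.9% | 5.2% |

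Further runs at 70% completion (1,500 per setting; r = 0.5, 0.6, 0.7, 0.8) gave 24.9, 23.2, 18.9 and 14.9% with the covariate against 14.4, 13.7, 10.7 and 9.0% without. The 250-trial set with complete data at r = 0.5 gave 27% against 22%. The covariate therefore adds about 6 to 10 points at 70% completion and 2 to 5 with complete data.

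**How often.** Under the assumed trigger, 5% of trials per outcome; for at least one of five, 1 − 0.95⁵ = 22.6% if they were independent.

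**The case against.** The article never says outright that an outcome's own baseline score enters its own model. A reader could take the rule to mean other scales, for example adjusting the worry model for an imbalanced stress score, which is harmless. A fuller analysis plan may settle this. That stands in part: own-score coverage is a reading. It is the natural one, though. The rule covers any score, nothing is excepted, and an outcome's own baseline is the most obvious candidate for adjustment.

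The objection on size is stronger. Most of the conditional false rejection (9-22%) is present without the covariate, so the full 15-27% must not be attributed to it. At 5% of trials per outcome, an added 6 to 10 points is 0.05 × 0.06 to 0.05 × 0.10, or 0.3 to 0.5 percentage points overall. The larger SE shortfall needs 30% missing data, and 70% completion is a target, not a forecast. The article also sets no significance level or efficacy decision rule; interval width is the fairer measure of harm.

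A reader might also infer that the main trial would be sized at a quarter to a third of what it needs, by comparing a model SD of 0.5-0.6 with 1.0. The article does not support that. It does not say planning SDs come from this model, and SDs of the observed scores are untouched. The comparison also sets an adjusted SD against a marginal one. Against a valid week-6 model, whose residual variance is 1 − r², the ratio at r = 0.5 is 0.4375/0.75 = 0.58 with complete data and 0.366/0.75 = 0.49 at 70% completion.

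**Conclusion.** The point holds as a wording fault with a definite consequence when it is triggered. The most robust result is the variance collapse: it follows from algebra for every correlation below 1, is large in every setting examined, and makes the adjusted model's variance unusable for the article's own planning objective. The SE understatement is secondary and depends on completion. The adjustment also fails in its purpose, because it leaves the regression-to-the-mean bias where it was.

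The figures rest on assumed correlations, equal SDs, data missing at random and a p<0.05 trigger. The documents do not support a claim that the article plainly prescribes this error, or that it alone produces the high conditional rejection rates. The analyses are secondary and exploratory in a pilot whose primary outcomes are descriptive, so this should be corrected but is of modest severity.

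**What to change.** In the section on secondary objectives, state that an outcome's own baseline score is never entered as a covariate in a model that has that score as a response. Where it is to be adjusted for, make the week-6 score the only response and the baseline score a covariate, preferably for all five outcomes whatever imbalance is observed. In simulation this gave SEs within about 3% of the empirical SD and rejection of 4.6-6.0% overall, and 5.0-5.2% after baseline imbalance. The exclusion sentence alone would remove the variance and SE fault but leave the regression-to-the-mean bias.

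Keep adjustment for other imbalanced characteristics or scores; striking scores from the rule altogether would remove valid adjustment too. Take planning SDs from the observed scores at each visit, or from the residual SD of the week-6 model if the main trial will use that analysis.

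The cost is two or three sentences and no new data. Participants without a week-6 score do not enter the week-6 model, so its analysis set should be described alongside the intention-to-treat statement.

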Week 3	Relating mindfully to emotions	• Emotions (28) • Mindful ways to regulate your emotions (193) • Practice of the week (28)	Working mindfully with emotions (10 min)	Noticing when caught up in emotions and practising coming back to the present moment
Week 4	Self-compassion	• Self-criticism (126) • Self-compassion (68) • Where does mindfulness come in (34) • Practice of the week (44)	Body, breath and sound (10 min)	Noticing when involved in self-criticism and practise using self-compassion
Week 5	Communicating mindfully	• Communication (93) • Practice of the week (51)	Body, breath, sound and thoughts (10 min)	During conversation, notice when the mind is caught up with other thoughts. Practise bringing attention back to the conversation
Week 6	Living mindfully	• The mindful pause (40) • Everyday mindfulness (52) • Meditation practice (29) • An ongoing experience (62)	Tuning into your surroundings (10 min)	Pause throughout the day (1-min practice). Get into the habit of watching the contents of your mind

Participants will receive an automatically generated email at the end of each week with a link to a brief questionnaire inquiring about their level of engagement with the program. Following completion of the questionnaire, participants will be directed to the website. Each topic of the program is explained through a short video ranging from 25 s to 3 min. The script of the videos is available for downloading and printing in PDF format so that participants can keep a copy of it should they wish to use it at a later stage. At the end of each video, participants will be reminded to continue with their daily meditation practice (formal practice) and will be given a specific mindfulness task to practise during their daily activities (informal practice).

To support participants with establishing a meditation routine, emails containing a link to a short, guided meditation audio file, voiced by co-author RC, will be sent twice daily. These emails will serve as reminders to meditate and will provide easy access to the meditation practice of the week.

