### Study discontinuation

Reasons for which participants may wish to discontinue the program may be varied, e.g. lack of time, lost interest in the program, or feeling too unwell. Participants who wish to discontinue will be invited to voluntarily inform the study team by email and provide reasons for discontinuation. Due to the self-guided, anonymous and automated nature of the intervention, the study team will not be able to initiate communication with participants who ceased interacting with the website.

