#### Adherence tracking and meditation log

Google Analytics will be used to track participants’ online activity, including login date/times, navigation patterns, page views and duration, and features used (video, audio and document downloads). At the end of each week, a set of three questions will capture information on any use of other types of meditation unrelated to the intervention, and frequency and duration of practice. Another three questions will estimate the amount of informal practice over the past week, and the specific use of the weekly topic, using a 5-point Likert scale.

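### Taking the larger of tracked and self-reported meditation time as the only exposure can distort the exploratory dose-response association; each source should also be analysed on its own.

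*Protocol article*

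**What the plan says.** Under Secondary objectives, the protocol article plans that a "potential association between overall meditation time and the secondary outcome measures will be assessed in the intervention group". The exposure is then fixed: "Weekly meditation time will be defined as the maximum between time collected from Google Analytics and time self-reported in the weekly questionnaires". No analysis by either source alone is named.

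The two sources are described under Adherence tracking and meditation log:

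- **Tracked:** "Google Analytics will be used to track participants’ online activity, including login date/times, navigation patterns, page views and duration, and features used", the features being video, audio and document downloads.
- **Self-reported:** three weekly questions on "any use of other types of meditation unrelated to the intervention, and frequency and duration of practice".

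The self-report depends on a response. In the section on the intervention group, "Participants will receive an automatically generated email at the end of each week with a link to a brief questionnaire", and on completing it participants are taken to the website. Under Study discontinuation, "the study team will not be able to initiate communication with participants who ceased interacting with the website".

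The section on randomisation says that participants know their allocation. The section on outcome measures shows that all five secondary outcomes are questionnaires filled in by the participant.

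**The concern.** A maximum is a one-sided rule. It can never fall below either source, so an over-report, or time with a page left open, survives whenever it is the higher value, and the lower value is discarded. Three consequences follow.

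1. In an answered week the exposure is the larger of two measurements. In an unanswered week only the tracked one exists. Two participants with the same practice can therefore receive different exposures because one answers more emails.
2. Self-report replaces the tracked value exactly when it is higher. If people who overstate practice also rate their wellbeing more favourably, exposure and outcome share an error.
3. If the reported duration includes outside meditation, the variable can switch from week to week between program use and total practice.

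At stake is the one planned analysis that links the amount of practice to outcome. The Discussion asks whether patients can learn from and benefit from the program without a therapist, so readers are likely to give that association some weight.

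**Working it through.** **Inputs from the protocol article.** The maximum rule (Secondary objectives); 14 scheduled sessions a week, which agrees with 2 × 7 (Primary objective); sessions of 5 min in weeks 1–2 and 10 min in weeks 3–6 (Table 1), so 14 × 5 = 70 and 14 × 10 = 140 min a week; a target of 50 intervention participants (Sample size); a 70% end-of-study completion target (Primary objective). The plan states no figure for the accuracy of either source, so there is none to reproduce.

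**Assumed, because not given.** Normal, independent errors with SD equal to 30% of each source's own mean; tracked mean 60–100% of true time; self-report mean 90–130% of true time; an unanswered week takes the tracked value.

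**Step 1: two unbiased sources with equal error SD s and error correlation ρ.**

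E[max] − μ = s × √((1 − ρ)/π)

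This gives 0.56s at ρ = 0, 0.47s at ρ = 0.3 and 0.36s at ρ = 0.6. Example: true practice is half the schedule in week 4, 70 min, so s = 0.3 × 70 = 21 min. At ρ = 0 an answered week is recorded on average as 70 + 0.564 × 21 = 81.8 min (+17%), and an unanswered week as 70 min.

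**Step 2: biased sources.** Let a and b be the self-report and tracked means relative to true time, θ = √((0.3a)² + (0.3b)²) and d = (a − b)/θ. Then

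E[max]/true = aΦ(d) + bΦ(−d) + θφ(d)

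For a = 1.3 and b = 1: θ = √(0.39² + 0.30²) = 0.492, d = 0.61, and E = 1.3 × 0.729 + 0.271 + 0.492 × 0.331 = 1.38. A simulation gave the same values:

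| Tracked mean / true | Self-report mean / true | Answered weeks | Unanswered weeks | Gap (points) |
|---|---|---|---|---|
| 1.0 | 1.0 | +17% | 0% | 17 |
| 1.0 | 1.3 | +38% | 0% | 38 |
| 0.8 | 1.0 | +7% | −20% | 27 |
| 0.8 | 1.3 | +33% | −20% | 53 |
| 0.6 | 1.0 | +2% | −40% | 42 |
| 0.7 | 0.9 | −4% | −30% | 26 |

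The sign in answered weeks varies. The gap is present in every row.

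**Step 3: effect on a real slope.** Take the six-week sum as exposure and let weekly response average about 70% and rise with practice. With unbiased sources, the fitted slope is about 0.80 of the true one under the maximum and 0.91 with tracked time. With tracking 20% low and self-report 30% high, the figures are 0.67 and 1.14. With tracking 40% low and unbiased self-report, they are 0.87 and 1.52. Neither exposure recovers the true slope.

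**Step 4: an apparent association.** A simulation with no true effect and an assumed tendency to over-report that is shared by exposure and outcome gave a correlation of about 0.07–0.09 under the maximum and about 0 with tracked time. The size depends wholly on how strong that tendency is assumed to be. For scale, 50 × 0.70 = 35 intervention participants with end-of-study scores give a standard error of about 1/√(35 − 3) = 0.18 for a correlation on Fisher's scale.

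**The case against.** The strongest defence is that the stated exposure is overall meditation time, and Google Analytics sees only what happens online. Audio can be downloaded, and practice need not involve the website. When one source can miss real practice, taking the larger value is a recognisable correction. The table supports this: with tracking 20–40% low and self-report unbiased, the maximum is within +2% to +7% in answered weeks, while tracked time is 20–40% low. In simulations the maximum usually correlated better with true time than tracked time did (about 0.73–0.95 against 0.59–0.93). This stands, and it means that simply replacing the maximum with tracked time would be a trade-off. It does not justify the maximum as the only exposure, because the correction works only in answered weeks and leaves the shared reporting error in place.

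It can also be said that participants who stop responding may lack end-of-study scores and so drop out of the association. That reduces the response problem but does not remove it, since those who answer intermittently remain. No weekly response rate is given.

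The questionnaire itself is not shown and may already ask about outside meditation as a separate item, so the mixing of two quantities is a possibility, not an established fault. How unanswered weeks are handled and the exact regression form may be in an analysis plan that is not shown, and they are not criticised here.

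**Conclusion.** The point holds as a modest one about an exploratory analysis. The rule is one-sided, its error depends on whether the weekly questionnaire is returned, and it prefers self-report exactly when that is higher, with outcomes from the same unblinded reporter. It can therefore distort the dose-response association or produce an apparent one. The 17 to 53 point gap and the spurious correlation of 0.07–0.09 rest on assumed error sizes. That correlation is also small beside a standard error of about 0.18.

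Two stronger readings are tempting and are not supported:

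- **That meditation time will necessarily be overstated.** This needs sources that are unbiased or too high on average. If both under-record, the recorded value can be too low, and unanswered weeks can pull the overall mean below the truth.
- **That program use will be overstated for the main trial.** The adherence rates under Primary objective count guided meditations listened to and videos viewed, and the maximum does not enter them. Nor does it enter the intention-to-treat mixed model.

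**What to change.** Do not rely on the maximum as the only exposure. Fit the association separately with:

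- tracked time, described as online program use; and
- self-reported time, with meditation unrelated to the program kept as its own variable.

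If the maximum is kept as a measure of overall practice, present it beside these two. State in advance that a dose-response will be interpreted only if it does not rest on self-report alone.

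The cost is a change of wording and one or two extra exploratory analyses. If the weekly items do not already separate program practice from other meditation, one would need clarifying. The downside is that tracked time alone misses offline practice, so a weak association with it would not rule out a benefit of untracked practice.
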